**Safety**

All patients who receive at least 1 dose of study medication will be included in the safety analysis. The prevalence of treatment emergent adverse events will be described using summary statistics and compared used the Chi-square test.

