**STUDY SYNOPSIS**

**Aims:**

**1)** Assess the clinical feasibility and utility of biweekly β-D-glucan testing as a guide for preemptive antifungal therapy in at-risk surgical intensive care unit (SICU) patients.

1. Evaluate the safety and tolerability of preemptive anidulafungin as compared to current practice (empiric antifungal therapy based on physician discretion) for the management of invasive candidiasis (IC).
2. Validate gene expression signatures predictive of IC.

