**Hypotheses:**

**1)** Biweekly β-D-glucan surveillance will identify SICU patients with an invasive fungal infection (IFI) before clinical signs or symptoms develop.

1. Anidulafungin initiated in response to a positive β-D-glucan test (i.e. preemptive therapy) will be well tolerated, safe, and effectively treat patients early, before advanced infection is established.
2. Peripheral blood gene expression signatures obtained serially from at-risk patients can predict early IC.

**Study Design:** Single center, randomized, non-blinded, parallel group, comparative study.

**Sample Size:** 100 subjects; 75 in the active surveillance/preemptive therapy arm and 25 in the usual care arm.

**Study Population:** Adult patients admitted to Duke University Medical Center SICU at-risk for the development of IC.

**Study Drug:** Intravenous anidulafungin initiated in response to a positive β-D-glucan test for subjects in the active surveillance/preemtpive arm. Preemptive treatment will continue for at least 14 days or until ICU discharge (maximum 28 days), which ever is longer.

**Efficacy:** IFI assessments will be made weekly and at SICU discharge.

**Safety:** A data safety monitoring board will review adverse events every 4 months.

**Statistics:** β-D-glucan test characteristics will be described using sensitivity, specificity, positive and negative predictive values. The proportions of patients developing proven or probable IC in each group will be compared using Fisher’s exact test. The prevalence of treatment emergent adverse events will be described using summary statistics. For gene expression analysis, we will designate subjects diagnosed with a *Candida* bloodstream infection as case patients and those who remained uninfected and had negative B-D-glucan testing as controls. Decision tree analysis will be used to develop predictive signatures for candidemia versus no infection.

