**Standard care/empiric therapy group**

Patients in the standard care arm will also have biweekly blood draws for the BDG assay until ICU discharge, but the test will not be performed in real-time. Specimens collected from subjects in this arm of the study will be batched and tested retrospectively. The clinicians, therefore, will be blinded to the BDG results and can not use the assay to inform treatment decisions. Because BDG test characteristics in SICU patients are not known, an essential aspect of this study is our ability to assess test performance in the population of interest in an unbiased fashion. Patients in the standard care group may receive antifungal prophylaxis and/or treatment at any time based on the discretion of the treating physician.

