**All Subjects**

The following procedures will be performed for all study subjects for the duration of the SICU stay:

- Serum red-top BDG and a PAX Gene tubes will be obtained 2 times/week (generally Monday and Thursdays) with the routine early morning blood work by the SICU nursing staff. Both phlebotomy tubes will be sent directly to the Duke Clinical Microbiology Laboratory. BDG results will be made available in real-time (within 24–72 hours) via a phone call directly to the clinician (surgical house staff and unit pharmacist) caring for the study subject assigned to preemptive therapy. BDG specimens obtained from patients assigned to empiric therapy (standard care) will be batched and tested at the end of study and the clinicians will not be made aware of the results. All RNA analyses will also be performed retrospectively for research purposes only.

*Patients in the active surveillance/preemptive therapy arm may have BDG testing performed on other days if the providers feel that the result would immediately impact initiation of antifungal therapy. The test will be available daily Monday through Friday.

- IFI assessments will be made weekly (EORTC/MSG criteria for proven or probable IFI will be applied [**Tables 3 & 4**]) and documented on the CRF.
- Supporting evidence of IFI obtained as part of routine care will be recorded weekly (i.e. routine laboratory testing, microbiology and blood culture results, imaging studies, biopsy reports) and documented on the CRF.
- Clinical risk factors for IC will be documented weekly (**Table 1**) and documented on the CRF.
- Factors known to be associated with false positive BDG tests will be documented weekly (**Table 2**) and documented on the CRF.
- Concomitant antimicrobials and immunosuppressive drugs will be documented weekly on the CRF.
- AEs will be recorded weekly and documented on a dedicated CRF.

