**STATISTICAL METHODOLOGY**

**Sample Size**

Targeted enrollment is 100 adult SICU patients. This study will not be powered to show a difference in the efficacy of preemptive management versus standard care due to single center population constraints in addition to cost limitations. Sample size calculations were therefore based on the number of adult patients expected to be admitted to the SICU over a 1 year period who are likely to meet inclusion criteria (n=700). Based on prior experience, it is reasonable to expect an accrual of 100 patients in a year. Using a 3:1 randomization strategy, 75 will be assigned to active surveillance and 25 to standard care. We estimate that 25% of patients will develop a positive test(13;25;27) and 19 will receive anidulafungin. These numbers should provide sufficient data for a preliminary feasibility evaluation of the preemptive strategy.

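### The safety analysis set holds only study-drug recipients, all from the preemptive arm, so the planned Chi-square comparison of adverse events with current practice has no comparator

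*Protocol*

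**What the plan says.** The Safety paragraph of the protocol's Statistical Methodology defines the set: "All patients who receive at least 1 dose of study medication will be included in the safety analysis". The next sentence says that the prevalence of treatment-emergent adverse events "will be described using summary statistics and compared used the Chi-square test". It does not name the groups to be compared.

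The synopsis defines the study drug as "Intravenous anidulafungin initiated in response to a positive β-D-glucan test for subjects in the active surveillance/preemtpive arm". The control arm is assigned no study drug: "Patients in the standard care group may receive antifungal prophylaxis and/or treatment at any time based on the discretion of the treating physician".

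The second synopsis aim is comparative. It is to evaluate the "safety and tolerability of preemptive anidulafungin as compared to current practice". The opening paragraph of Study Objectives likewise sets the feasibility and safety of the strategy against standard care. Primary objective 3 and primary endpoint 3, by contrast, name the safety and tolerability of preemptive anidulafungin without a comparator, and the synopsis statistics paragraph plans summary statistics only.

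The Sample Size section expects that "19 will receive anidulafungin". The Data Analysis section puts every primary and secondary analysis on an intent-to-treat footing. Under All Subjects, the procedures state that "AEs will be recorded weekly and documented on a dedicated CRF".

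**The concern.** Safety is one of three primary endpoints, and the aim behind it asks how preemptive anidulafungin compares with current practice. The Safety section admits only one side of that comparison. An analyst who follows it literally has recipients from one arm and nobody from the other.

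The likely improvisation is to set the recipients against all standard-care patients. That would give a p-value, but randomisation would no longer protect the contrast. It would also leave out the preemptive patients who are monitored but never dosed, although the main goal concerns the safety of the whole strategy. Adverse events are recorded weekly in both arms, so the restriction discards comparator data that the trial will hold.

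**Working it through.** **Inputs from the protocol.** 100 patients randomised 3:1; 25% expected to test positive; about 19 expected to be treated (Sample Size). Two-sided 5% level (Statistical Analyses). Safety set: at least one dose of study medication (Safety).

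**Input not in the protocol.** It gives no control adverse event rate, so the power figures assume 10 to 50%.

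**1. Reproduce the plan's figure.** Preemptive arm: 100 × 3/4 = 75. Recipients: 75 × 0.25 = 18.75, rounded to 19. This agrees with the protocol. If the 25% rate is true, the 95% binomial range is 12 to 26 recipients.

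**2. Safety set by arm.**

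| | Randomised | In safety set as written |
|---|---|---|
| Preemptive | 75 | about 19 |
| Standard care | 25 | 0 |

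One margin of the arm-by-event table is zero, so its expected counts are zero and the Chi-square statistic is undefined. About 75 − 19 = 56 preemptive patients also fall outside the set. A control patient given an antifungal by the treating physician is not receiving study medication as defined, so does not enter it.

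**3. Recipients versus all controls (19 versus 25).** Entry on one side requires a positive BDG result, known only after allocation. No such condition applies to the other side. The groups are therefore not comparable by randomisation. At the assumed control rates, power for a 20-point excess would be only about 26 to 40%.

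**4. All randomised patients by arm (75 versus 25).**

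| Assumed control rate | Preemptive-arm rate needed for 80% power | Power for a 20-point excess |
|---|---|---|
| 10% | 38% | 52% |
| 20% | 51% | 44% |
| 30% | 62% | 41% |
| 40% | 72% | 41% |
| 50% | 80% | 44% |

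Dilution: if the drug adds D points in recipients and the strategy changes nothing in the others, the arm-level excess is about 0.25 × D. A 20-point excess in recipients becomes 0.25 × 20 = 5 points by arm.

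**5. Is Chi-square adequate by arm?** The expected control count is 25 × pooled incidence. It falls below 5 when pooled incidence is under 5/25 = 20%. Chi-square is thus doubtful for the less common events, not for all. The protocol already uses Fisher's exact test for invasive fungal infection.

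**6. Precision of the recipient summary.** With 0 events in 19, the exact two-sided 95% upper limit is 1 − 0.025^(1/19) = 17.6%. With 4 in 19 (21%), the exact 95% interval is 6% to 46%. An event with true incidence 10% goes unseen with probability 0.9^19 = 13.5%. These figures follow from the number exposed and do not change under the repair.

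**The case against.** The strongest reply is that the primary safety endpoint is not comparative. Objective 3, endpoint 3 and the synopsis statistics paragraph are all descriptive, the Sample Size section calls the study a preliminary feasibility evaluation, and a dosed-only set suits tolerability. This stands. A reader might infer that the primary safety endpoint cannot be analysed at all. It can, because summary statistics in about 19 recipients are computable and valid. Only the added comparison fails.

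It can also be said that a by-arm analysis is already implied, or that a statistical analysis plan may name the groups. The intent-to-treat sentence does point that way. Mortality by group, the interim review of differences between arms, and the conditional safety listing of dropouts by group cover part of the ground. It would therefore be too strong to say that no by-arm safety look is foreseen. But the general intent-to-treat rule contradicts the specific Safety rule, and nothing reconciles them. An analysis plan could supply a comparator only by departing from the set that the protocol fixes.

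Two further inferences go beyond the text. One is that recipients are sicker or later in their stay than controls. The protocol gives no such data, and the first BDG sample is drawn at randomisation, so a patient can be positive from the start. The loss of randomisation does not depend on it. The other is that controls who test positive retrospectively form a fair unexposed group. At the same 25% rate there would be 0.25 × 25 = 6.25, about 6, and they may receive antifungals at any time.

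The objection that a by-arm comparison has its own biases also stands. Weekly liver tests and physical examinations are scheduled only on anidulafungin. Follow-up runs past SICU discharge only for patients still on study drug. After discontinuation the protocol promises only mortality follow-up, and one discontinuation criterion applies to the preemptive arm alone.

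**Conclusion.** The point holds for the comparison, not for the description. By design the stated safety set contains about 19 preemptive patients and no standard-care patients, so the stated Chi-square comparison cannot be computed on it. It cannot serve the aim of comparing with current practice, and it conflicts with the intent-to-treat rule. The absence of controls follows from the definition of study drug and rests on no assumption. The figure of 19 rests on the protocol's 25% positive rate.

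The 17.6% limit and the 13.5% chance of missing an event might be taken as the size of this defect. They are not: they describe a small exposed group and would be the same under a corrected plan. The power figures depend on assumed control rates and show that even a correct by-arm comparison detects only large differences.

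**What to change.** Amend the Safety section to define two analyses.

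1. **Comparison with current practice.** Use all randomised patients by assigned arm (planned 75 versus 25), counting adverse events from randomisation to SICU discharge in both arms. Report risk differences with exact 95% intervals, and use Fisher's exact test where expected counts are small. Label the comparison descriptive.
2. **Tolerability of anidulafungin.** Summarise the roughly 19 recipients separately with exact 95% intervals and no test. Events after SICU discharge in patients still on study drug belong here, not in the by-arm comparison.

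Reconcile the second synopsis aim, the Safety section and the intent-to-treat sentence under Data Analysis, so that each analysis has one stated population. Any contrast with the roughly 6 retrospectively BDG-positive controls should be called exploratory.

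The cost is wording and a few tables, since adverse events are already recorded weekly in all subjects. The plan should state three limits:
- The by-arm contrast dilutes a drug effect to about a quarter and has low power.
- Scheduled weekly liver tests and examinations on anidulafungin make detection unequal between arms.
- Adverse event data may be lost after discontinuation, where only mortality follow-up is promised and one criterion is specific to the preemptive arm.

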**DESCRIPTION OF STUDY END POINTS**

**Primary Endpoints**

1. Feasibility of preemptive monitoring strategy.
2. β-D-glucan test performance in the stand care (empiric therapy) group.
3. Safety and tolerability of preemptive anidulafungin.

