**Statistical Analyses**

Statistical analysis will be performed using SAS software. P values and 95% confidence intervals will be 2-tailed and statistical significance set at the 5% level unless otherwise specified.

*Demographics and Baseline Characteristics*

Demographic and baseline characteristic information will be summarized and compared using the Chi-squared test for discrete variables and one way ANOVA for continuous various to assess any imbalance between treatment groups.

*β-D-glucan Test Characteristics*

β-D-glucan test characteristics, using data collected from standard care group, will be described using sensitivity, specificity, positive and negative predictive values. Proven and probable cases of IFI, as defined by EORTC/MSG criteria (**tables 3 and 4**), will constitute the standard for comparison.

*Feasibility Analysis*

Feasibility will be a description of preemptive protocol adherence, BDG test requests off schedule, and the number of patients withdrawn from the preemptive arm due to the initiation of empiric systemic antifungal therapy in the absence of a positive BDG test.

*Efficacy End-Points*

Development of IFI during the study period will be assessed by the principal investigator (PI) and a second blinded investigator using predefined EORTC/MSG criteria for proven or probable disease. The study period is defined as the time the patient was cared for in the SICU. The proportions of patients developing IFI, and IC specifically, in each group will be compared using Fisher’s exact test. The median ICU stay and number of febrile days while in the ICU will be compared using the Kruskal-Wallis test. Patient mortality, overall and attributed to IFI, will also be summarized by group. Response-to-therapy (RTT) will be determined by the PI and a blinded second investigator. The RTT population will consist of all patients who were underwent BDG monitoring for at least 3 days and received at least 1 dose of systemic antifungal therapy.

*RNA Analyses*

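### Primary safety endpoint: the only test named for adverse events is a Chi-square difference test, which with about 19 treated patients cannot support a hypothesis that the drug is safe; exact intervals should carry the safety statement

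*Protocol*

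**What the plan says.** Under Primary Endpoints the protocol lists "Safety and tolerability of preemptive anidulafungin". The matching hypothesis in the synopsis is that anidulafungin started on a positive β-D-glucan test "will be well tolerated, safe, and effectively treat patients early".

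The Safety section under Statistical Methodology defines the analysis set: "All patients who receive at least 1 dose of study medication will be included in the safety analysis". It then gives the analysis: "The prevalence of treatment emergent adverse events will be described using summary statistics and compared used the Chi-square test". The Statistical Analyses section supplies the general rule: "P values and 95% confidence intervals will be 2-tailed and statistical significance set at the 5% level unless otherwise specified".

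On numbers, the Sample Size section says: "Using a 3:1 randomization strategy, 75 will be assigned to active surveillance and 25 to standard care". It adds: "We estimate that 25% of patients will develop a positive test(13;25;27) and 19 will receive anidulafungin". That section states that the study is not powered for efficacy. It states no power, detectable difference or acceptable rate for adverse events.

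**The concern.** A hypothesis that a drug is safe claims that harm is absent or small. A test of no difference cannot confirm such a claim. It can contradict it when p falls below 0.05, but with a small sample p above 0.05 is compatible both with no harm and with a substantial excess. What can support the claim is a limit on how high the event rate, or the excess over a comparator, could plausibly be. The Safety section names the difference test and asks for no such limit.

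If the section is followed as written, primary endpoint 3 yields a table of adverse-event percentages and p-values. A reader may take non-significant p-values as reassurance that the data do not provide. What 19 treated patients can exclude would go unreported.

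**Working it through.** **Inputs from the protocol.** 100 patients randomised 3:1, so 75 and 25. Expected to be treated: 0.25 × 75 = 18.75, which rounds to the stated 19. Two-sided 5% level, Chi-square test.

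**Inputs assumed.** The protocol gives no background adverse-event rate, so 10%, 20% and a few higher rates are used. It does not say who the treated patients are compared with, so four readings are tried:
- 19 treated v 25 standard care
- 75 v 25, by randomised arm
- 19 treated v 75 − 19 = 56 untreated surveillance patients
- 19 treated v 56 + 25 = 81 untreated patients in all

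**Miss rate.** With a events among n₁ patients and b among n₂, and N = n₁ + n₂, the uncorrected statistic is

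X² = N·[a(n₂ − b) − b(n₁ − a)]² / [n₁·n₂·(a + b)·(N − a − b)].

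The test rejects when X² ≥ 3.84. The miss rate is 1 minus the sum, over all rejecting pairs (a, b), of Bin(a; n₁, p₁) × Bin(b; n₂, p₂). This is exact enumeration.

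| Background → raised rate | 19 v 25 | 75 v 25 | 19 v 56 | 19 v 81 |
|---|---|---|---|---|
| 10% → 20% | 83% | 83% | 78% | 74% |
| 20% → 40% | 72% | 55% | 59% | 54% |
| 10% → 30% | 59% | 47% | 46% | 40% |
| 15% → 45% | 43% | 18% | 26% | 20% |
| 30% → 60% | 47% | 23% | 35% | 30% |
| 20% → 60% | 22% | 4% | 10% | 7% |
| 40% → 80% | 19% | 4% | 12% | 8% |

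The 75 v 25 column refers to the rate in the whole arm, of whom only 19 are treated. If the other 56 stay at a 10% background, an arm rate of 20% needs (0.20 × 75 − 0.10 × 56) / 19 = 9.4 / 19 = 49% among the treated. The larger arm therefore does not make the by-arm reading sensitive to a drug effect.

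**Size of the test.** Setting p₁ = p₂ in the same enumeration gives the true type I error:
- At a 2% event rate: 0.4% (19 v 25), 2.4% (75 v 25), 2.0% (19 v 56) and 8.2% (19 v 81), against a nominal 5%.
- At 10% and 20%: between 4.0% and 4.8% in all four layouts.

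The approximation is therefore a problem for rare events only.

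**What 19 treated patients can exclude.** The two-sided 95% Clopper-Pearson upper limit p solves P(X ≤ x | n = 19, p) = 0.025.
- x = 0: (1 − p)¹⁹ = 0.025, so p = 1 − 0.025^(1/19) = 17.6%.
- x = 1: (1 − p)¹⁹ + 19p(1 − p)¹⁸ = 0.025, so p = 26.0%.

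**The case against.** **No misreading is planned.** A reader might infer that the protocol intends to declare safety from p > 0.05. It does not say so. The Safety section puts summary statistics first, and the synopsis mentions only the descriptive summary. This stands, and the point is limited accordingly: the stated test is the wrong tool for the stated hypothesis, and no better one is tied to adverse events.

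**Intervals are already foreseen.** The Statistical Analyses section mentions 95% confidence intervals in general terms, and interval methods can be left to an analysis plan that is not shown. This stands in part. The absence of a named interval method is no fault in itself. However, the protocol has itself fixed an inference for this primary endpoint, and that choice can be judged.

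**It is a feasibility study.** Low power alone is not an error, because no power for safety is claimed. The caveats in the text, however, concern efficacy in the Sample Size section, and infection and mortality in the interim analysis section. None covers adverse events. A small preliminary study is also where estimation serves better than testing.

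**The test is not blind to large effects.** A reader might infer that any doubling or tripling goes unseen. The table does not support that. A tripling from 10% is missed 59% of the time at 19 v 25, but 40% to 47% with the other comparators. From 20% it is missed 22% of the time or less. A doubling from 40% is missed 19% of the time or less.

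**Replacing Chi-square with Fisher's test is no cure.** The protocol uses Fisher's exact test for infection, so a switch is tempting. It would lower power further: for 10% → 30% at 19 v 25, from 41% to 31%.

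**Conclusion.** The point holds in this form. For a primary endpoint whose hypothesis is that the drug is safe, the protocol names a difference test and ties no bound to adverse events. With about 19 treated patients, a non-significant result is weak evidence either way for moderate increases. Across the four comparators, 10% → 20% is missed 74% to 83% of the time, 20% → 40% is missed 54% to 72%, and 10% → 30% is missed 40% to 59%. Increases as large as 20% → 60% are mostly detected. For events near 2% the size of the test is also unreliable, from 0.4% to 8.2%.

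These figures rest on assumed background rates and comparators, on 19 patients being treated as the protocol expects, and on the uncorrected Chi-square. The 17.6% and 26.0% limits depend only on the number treated and the events seen.

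The documents do not support saying that the trial would very likely miss every important excess, or that its authors plan to equate non-significance with safety. The change is worth making because the remedy is cheap and answers the question that the hypothesis asks.

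**What to change.** In the Safety section, replace the Chi-square comparison as the basis for the safety statement:

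- Report each adverse-event rate and each liver-function abnormality rate among treated patients with an exact (Clopper-Pearson) 95% interval.
- Give any between-group comparison as a risk difference with an exact or score-based 95% interval, and name the comparison group.
- State that this comparison is unpowered and that a non-significant result is not evidence of safety.
- State what the data can exclude, for example that with 19 treated patients no events exclude only rates above 17.6%, and one event only rates above 26.0%.

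The cost is one paragraph of analysis wording, with no change to enrolment, design or treatment. The downside is a more modest safety statement.
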